**Table tab3:** 

Current medication at time of blood sampling	
ACE inhibitor	Y/N
AT2 receptor blocker	Y/N
Beta blockers	Y/N
Corticoids	Y/N
Immunosuppressive medication	Y/N
Platelet inhibition	Y/N
Dual platelet inhibition	Y/N, name of drug, dose
Oral anticoagulation therapy	Y/N, name of drug, dose
Time of last intake	Date, time
Other anticoagulation drugs	Name of drug
Unfractionated heparin	Dose
Low molecular weight heparin	Dose
Other anticoagulation drug	Dose

**Table tab4:** 

Condition at time of blood collection	
Ventilated/tracheotomized	Y/N
Glasgow-Coma-Scale	Number
paO_2_	Number
FiO_2_	Number
Blood pressure systolic	Number
Blood pressure diastolic	Number
Blood pressure mean	Number
Heart rate	Number
Catecholamine	Name of drug
Catecholamine dose	Number
Inotropic	Name of drug
Inotropic	Dose
Bilirubin	Number
Thrombocytes	Number
Creatinine	Number
Body temperature	Number
Breathing rate	Number
pH value	Number
Sodium	Number
Potassium	Number
Bicarbonate	Number
Hemoglobin	Number
Hematocrit	Number
Leukocytes	Number
ECMO therapy	Y/N
Date and time of ECMO initiation	Date, time
D-dimer number	Number
Leukocytes	Number
C-reactive protein	Number
Procalcitonin	Number

**Table tab5:** 

Complications during the last 24 h before blood sampling	
Bleeding	Y/N, date
Type of bleeding	Text
Blood loss	ml
Blood products, packed red blood cells	Y/N, number
Blood products, fresh frozen plasma	Y/N, number
Blood products, platelet concentrate	Y/N, number
Blood products, 4-factor concentrate	Y/N, number
Blood products, other	Y/N, name, number

*Demographic data of healthy participants:*

**Table tab6:** 

Date of blood collection	Date, time
Date of birth	Date
Size	Number
Weight	Number
Gender	m/f/d

#### Timeline

2.7.6

The study is planned to run over a total period of 2 years, with a recruitment phase lasting 9 months.

#### Sample size and statistical analysis

2.7.7

The primary objective of this study is to assess whether the area under the curve (AUC), as a measure of the forces exerted by the pneumatic tube system (PTS), has a clinically significant effect on coagulation analyses with the VET. The parameter used for sample size calculation is the clotting time (CT), a test result of viscoelastic testing. The primary endpoint for the sample size calculation is the binary outcome of a clinically significant change in CT. Clinical significance is defined on the basis of established treatment algorithms used in routine clinical practice (2). In these treatment algorithms, a CT change of ≥20 s in the ClotPro^®^ ExTest significantly influences therapeutic decisions and is thus considered clinically relevant. To enhance the level of safety, in this study a clinically significant difference was defined as a change in CT of ≥10 s between manual transport and PTS transport. A logistic regression model is employed for the sample size calculation, with the binary outcome of a clinically significant change as the dependent variable. We plan to perform the analysis after the completion of the study via logistic regression as well. The independent variables will be the AUC in both cohort (healthy participants vs. critically ill septic patients). Owing to the lack of prior data for sample size planning via ClotPro^®^, estimates will be derived from published data on ROTEM^®^. Given the similar underlying principles of both devices, these data can reasonably be applied for sample size estimation.

The sample size calculation is based on estimating the probability of the primary endpoint under two conditions (H_0_ and H_1_). Since direct probability estimates for H_0_ and H_1_ are unavailable, literature data for CT are used:

H₀ (Null Hypothesis): The probability of a clinically relevant CT change when the AUC is at its mean value, i.e., manual transport, where no significant effect is expected. The probability of a clinically relevant CT change due to manual transport is considered very low. On the basis of Martin et al. (10), this probability is estimated at 0.045.H₁ (Alternative Hypothesis): The probability of a clinically relevant CT change when the AUC is at its mean plus one standard deviation, i.e., PTS transport, where an effect is expected. The probability of a clinically relevant CT change due to increased AUC in PTS transport can be inferred from the method established by Streichert et al. (28). On the basis of the mean difference and standard deviation of CT changes between transport methods in Martin et al. (10), this probability is estimated at 0.21.

Sample size calculation was performed via G-Power 3.1 (29) with the following parameters: significance level (*α*) = 0.05; power (1-*β*) = 0.8; two-sided test; R^2^ other X = 0.36; Wald’s Z test. The total required sample size was determined to be N = 83 paired comparisons (manual vs. PTS transport). Considering potential dropouts due to sampling errors, withdrawal of consent, or failures in point-of-care testing, a dropout rate of 10% is assumed, increasing the total required sample size to 92. The participants will be equally distributed between the two study groups, resulting in 46 cases per group (e.g., healthy volunteers and critically ill septic patients).

Baseline comparisons between the two cohorts will be conducted via t tests for normally distributed data and the Wilcoxon test when normality is violated. Normality will be assessed via the Shapiro–Wilk test. A *p* value ≤ 0.05 was considered statistically significant. All the statistical analyses will be performed via MATLAB software (The MathWorks Inc., 2024).

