**Study design:**

This prospective, randomized clinical trial includes both healthy volunteers and critically ill septic patients. Paired blood samples are collected and randomly assigned to either manual or PTS transport, with each subject serving as their own control. Acceleration forces during PTS transport are continuously recorded using a three-axis accelerometer. Samples are analyzed using standard lab tests and following point-of-care devices: ClotPro^®^, ROTEM^®^ sigma, Multiplate^®^, and TEG6s^®^. The primary outcome is the difference in coagulation parameters between transport methods, evaluated in the context of measured acceleration forces.

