### Trial objectives

2.1

The Viscoelastic Testing after Pneumatic Tube Transport (VETaPT) trial study investigates whether PTS transport has a clinically significant impact on coagulation results obtained from of three next generation POC VET devices and platelet function testing in healthy volunteers and critically ill septic patients. The primary outcome is the difference in test results between manually and PTS-transported blood samples in both healthy volunteers and critically ill septic patients.

As secondary objectives, the study explores whether the magnitude of acceleration forces during PTS transport correlates with changes in coagulation parameters and whether this effect differs between healthy and septic individuals due to sepsis-associated coagulation alterations. In addition, the study aims to define a threshold of PTS-induced forces beyond which clinically relevant deviations in test results occur. The study’s area under the curve (AUC)-based method may enable the findings to be extrapolated to other PTS systems without requiring further blood sample transport and analysis. Such a threshold could help establish safe transport conditions and enable the generalization of results to other PTS systems using force measurements alone, without the need for additional blood sample testing.

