This study is the first to simultaneously compare multiple next generation VET devices while distinguishing between healthy volunteers and sepsis patients and to conduct precise quantification of acceleration forces during PTS transport.

The findings of this study can contribute to the safe application of PTS for the transport of blood samples for VET analyses. This allows for faster transport with reduced personnel requirements, leading to quicker results and earlier initiation of therapies. Moreover, these findings may serve as a foundation for further studies on coagulation activation in extracorporeal circulation settings.

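### Sections 2.1 and 2.7.7 name different primary questions, and the one outcome analysis stated, an AUC regression across pairs, does not test the average manual-versus-PTS difference

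*Protocol article*

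**What the plan says.** - **Section 2.1 (Trial objectives):** "The primary outcome is the difference in test results between manually and PTS-transported blood samples", in both cohorts. The acceleration question ranks lower: "As secondary objectives, the study explores whether the magnitude of acceleration forces during PTS transport correlates with changes in coagulation parameters".
- **Abstract (Study design):** "The primary outcome is the difference in coagulation parameters between transport methods, evaluated in the context of measured acceleration forces".
- **Section 2.7.7 (Sample size and statistical analysis):** "The primary objective of this study is to assess whether the area under the curve (AUC"), as a measure of PTS force, has a clinically significant effect. The endpoint is binary, "a change in CT of ≥10 s between manual transport and PTS transport". On the model: "We plan to perform the analysis after the completion of the study via logistic regression as well". On the covariates: "The independent variables will be the AUC in both cohort (healthy participants vs. critically ill septic patients").
- **H₀ and H₁ in section 2.7.7:** mean AUC is labelled as manual transport (event probability 0.045), and mean plus one SD as PTS transport (0.21). The sample size is 83 manual-versus-PTS pairs.
- **Other tests in section 2.7.7:** the t and Wilcoxon tests compare the two cohorts at baseline, not the two transport modes.

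**The concern.** The article gives two different primary questions. The first is whether PTS results differ from manual results. The second is whether, across transports, more force goes with more frequent CT changes. An effect can be present on the first and absent on the second.

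The only outcome analysis described addresses the second. A non-significant AUC slope could therefore be reported as the primary result although PTS results differ from manual results by a similar amount in every pair. A significant slope would not give the size of the average difference either. Section 2.1 calls that difference primary, and a hospital deciding whether to use its tube system needs it.

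**Working it through.** **1. What the model can estimate.** The outcome needs both samples of a pair, so there is one outcome per pair. Section 2.2 records acceleration on PTS runs, and section 2.6 relates AUC to the differences between transport methods. For pair i the model is

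logit P(Yᵢ = 1) = b₀ + b₁·AUCᵢ + b₂·cohortᵢ, with Yᵢ = 1 if |CT_PTS − CT_manual| ≥ 10 s.

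There is no transport-mode term and none is possible, because the contrast is already inside Y. If PTS shifts every CT by δ and the paired difference has SD σ, then

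P(Y = 1) = Φ((−10 − δ)/σ) + 1 − Φ((10 − δ)/σ).

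This does not contain AUC, so b₁ = 0 for any δ. The shift goes into b₀, for which the article states no test and no reference value.

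**2. The H₀/H₁ labels.** A manual sample has no manual-versus-PTS change of its own, so it cannot be an observation in this model. The mean AUC over pairs is the mean over PTS runs. Section 2.6 also sets the AUC cutoff at the acceleration typical of manual transport, which puts manual transport near the bottom of the AUC scale rather than at its mean.

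**3. The plan's own sample size.** The odds ratio is (0.21/0.79)/(0.045/0.955) = 5.64, and ln 5.64 = 1.730. The Hsieh formula, two-sided, gives

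(1.960 + 0.842)² / [0.045 × 0.955 × 1.730²] / (1 − 0.36) = 95.3, so 96.

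The Demidenko Wald method with normal X gives 103 two-sided and 81 one-sided. The stated 83 was not reproduced as a two-sided figure. The distribution of X is not stated, so this is a separate matter and nothing below depends on it. What matters here is that 83 was derived for the AUC slope.

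**4. Simulation of an effect flat in AUC.** The planned model (AUC and cohort) was fitted to 83 pairs in 1,000 to 4,000 runs. The paired SD is not in the article, so 5 to 15 s is assumed. With SD 5 s, the 0.045 rate would be pure zero-mean normal noise (10/2.005 = 4.99 s).

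| SD (s) | Shift (s) | Event rate | AUC slope rejects | Paired t rejects |
|---|---|---|---|---|
| 5 | 5 | 0.16 | 4.5% | 100% |
| 5 | 10 | 0.50 | 3.2% | 100% |
| 5 | 15 | 0.85 | 4.8% | 100% |
| 8 | 5 | 0.30 | 4.2% | 99.8% |
| 8 | 10 | 0.51 | 6.2% | 100% |
| 8 | 15 | 0.73 | 5.1% | 100% |
| 10 | 5 | 0.38 | 4.8% | 99.3% |
| 10 | 10 | 0.52 | 4.5% | 100% |
| 10 | 15 | 0.70 | 4.7% | 100% |
| 15 | 5 | 0.53 | 3.9% | 84.2% |
| 15 | 10 | 0.59 | 3.6% | 100% |
| 15 | 15 | 0.68 | 4.6% | 100% |

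With event rates set directly, flat in AUC at 0.21, 0.50 and 0.80, the slope test rejects in 4.3%, 5.0% and 5.1% of runs. Under the plan's own slope it rejects in about 94% (simulated without the R² = 0.36 correlation). The test works for the question it asks.

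**5. Precision of a paired analysis.** The half-width is t × SD/√n.

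- 83 pairs: 1.99 × 5/√83 = 1.1 s, and 1.99 × 15/√83 = 3.3 s.
- 41 per cohort: 2.02 × 5/√41 = 1.6 s, and 2.02 × 15/√41 = 4.7 s.
- Detectable mean difference at 80% power: 2.80/√83 = 0.31 SD.

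**6. Why ±10 s cannot serve as a margin for the mean.** Take a mean shift of 8 s and SD 5 s. The 95% CI is 8 ± 1.1, about 6.9 to 9.1 s, wholly inside ±10 s. Yet P(d ≥ 10) = P(Z ≥ 0.4), about 34% of pairs, which exceeds the plan's own H₁ rate of 0.21.

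**The case against.** The regression's outcome is itself the manual-versus-PTS difference, and the abstract ties that difference to measured acceleration. Section 2.1 names an outcome and section 2.7.7 an objective, so the conflict is narrower than two rival endpoints. The article condenses a fuller document and does not say that the regression is the only outcome analysis. The trial expects an effect that rises with force and deliberately varies speed and sample fixation to spread AUC. With no slope, a slope test rejects at alpha by construction.

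Much of this stands. If the effect rises with AUC over the observed range, the planned test can detect it. The failure is confined to effects that are flat over that range, for example ones already saturated at the gentlest PTS run. The simulation shows a consequence of the model and says nothing about how likely a flat effect is. That the slope compares only PTS runs follows from the pair-level outcome and the PTS-run AUC; the article does not say so in words.

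What does not stand is that the abstract's wording or the H₀/H₁ labels supply a test of the average difference. The abstract names no test, and the labels describe a contrast that the model cannot contain. The ranking conflict is in the stated text and is not detail left to a fuller document.

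A reader might also infer that the Discussion rests safety on a null slope. It says only: "The findings of this study can contribute to the safe application of PTS for the transport of blood samples for VET analyses". The route to safety in section 2.1 is a force threshold.

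**Conclusion.** The point holds in this form: the primary question differs between sections 2.1 and 2.7.7, and the outcome analysis stated in 2.7.7 does not test the average manual-versus-PTS difference that 2.1 makes primary. For an effect flat over the observed AUC range, the stated test rejects in about 3–6% of runs with 83 pairs. This rests on one outcome and one PTS-run AUC per pair, and on an assumed paired SD of 5 to 15 s.

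A reader might infer that a large uniform PTS effect would go unseen. The article does not support that, because an event rate of 50% or 80% would be plain descriptively. What is missing is a reference rate or rule to judge it by. Section 3 concedes that device precision cannot be assessed, so the trial itself cannot separate the raw rate from measurement noise. A signed mean difference is less exposed to this, since symmetric noise averages out.

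A reader might also take the narrowest precision figure (about 1.1 s) as settled. It depends on one assumed SD, and the range in the working should be quoted instead.

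**What to change.** 1. State one primary objective, the same in sections 2.1 and 2.7.7.
2. In 2.7.7, add as the analysis of the section 2.1 primary outcome the signed paired difference (PTS minus manual) in ClotPro ExTest CT: mean with 95% CI, overall and per cohort. Report with it the proportion of pairs changing by 10 s or more, with exact CI.
3. Keep the AUC logistic regression as the key secondary, dose-response analysis. Say that N = 83 was derived for it, and correct the manual and PTS labels in H₀ and H₁.
4. Do not use ±10 s as an equivalence margin for the mean, because the plan defines it for one pair's change. Rest any conclusion of no clinically relevant effect on the proportion of pairs changing by 10 s or more, or on a separately justified margin, and not on a non-significant AUC slope.

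The cost is wording in 2.7.7 and the analysis plan, plus a short precision statement beside the sample size, since 83 was not derived for the paired analysis. The paired samples are already part of the design, so no further samples or participants are needed.

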
Does the actual transport speed match the manufacturer’s specifications?How long is the blood sample exposed to this speed?What acceleration forces occur at the start and end of transport?Is there a correlation between the magnitude of the acceleration forces and alterations influence in POC parameters?Is the observed effect clinically meaningful, or is it merely statistically significant?

Therefore, precise quantification of the forces acting within a PTS is essential for understanding their potential impact on blood samples. This study hypothesizes that transport of blood samples via a PTS has a clinically significant impact on results obtained from next generation VET devices. This effect is expected to correlate with the magnitude of acceleration forces during transport and may differ between healthy individuals and critically ill septic patients due to sepsis-associated coagulation abnormalities.

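### Whether septic samples are more susceptible to transport force is a difference in AUC slope between cohorts, but the only outcome model stated names no comparison of slopes and uses a fixed 10 s event that also responds to noise

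*Protocol article*

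**What the plan says.** Section 2.1 (Trial objectives) lists as secondary questions whether force correlates with changes in coagulation parameters and "whether this effect differs between healthy and septic individuals due to sepsis-associated coagulation alterations". The Introduction states the matching hypothesis, that the effect "may differ between healthy individuals and critically ill septic patients due to sepsis-associated coagulation abnormalities". The abstract's Objective and the Discussion repeat the question in terms of susceptibility to acceleration.

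Section 2.7.7 gives the only outcome model. The dependent variable is binary, a CT change of 10 s or more between manual and pneumatic tube transport, with the same cut in both cohorts. The model is logistic regression, both for planning and for the final analysis. On covariates it says: "The independent variables will be the AUC in both cohort (healthy participants vs. critically ill septic patients". It names no product term and no test between slopes. The other comparison of cohorts in that section is of baseline data.

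The sample size uses "significance level (*α*) = 0.05", "power (1-*β*) = 0.8" and "two-sided test; R^2^ other X = 0.36". For the event at mean AUC, "this probability is estimated at 0.045"; for mean plus one SD, "this probability is estimated at 0.21". The result is 83 pairs for one AUC coefficient in both cohorts together, raised to 92 for dropout (46 per cohort).

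**The concern.** Susceptibility to force means that the same increase in AUC moves CT further in septic samples. In a regression this is the AUC-by-cohort term. The covariate sentence can be read in two ways, and neither gives that test.

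- **AUC and cohort as main effects.** The cohort coefficient compares how often the 10 s line is crossed at equal AUC. It can be non-zero when the AUC slopes are identical, or when AUC has no effect at all.
- **A separate AUC slope per cohort.** The slopes are estimated, but no comparison between them is stated.

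A fixed absolute cut adds a second problem. The chance of crossing 10 s depends on the spread of the paired difference as well as on its mean. Section 2.3 requires anticoagulation at any dosage in septic patients and no recent medication in volunteers, so unequal spread is plausible. The Discussion concedes that device precision cannot be assessed within the trial. A cohort effect on the 10 s event could therefore be reported as greater susceptibility when it reflects noise, and a real slope difference could be missed.

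**Working it through.** **1. The plan's own figure.** The log-odds slope is ln(0.21/0.79) − ln(0.045/0.955) = 1.730, an odds ratio of 5.64 per SD of AUC. With standard normal AUC and division by 1 − 0.36 = 0.64, the two-sided requirement depends on the formula:
- Hsieh: (1.960 + 0.842)² / (0.045 × 0.955 × 1.730²) / 0.64 ≈ 95.3, so 96.
- Demidenko without variance correction: 102.8, so 103.
- Demidenko with variance correction: 58.1, so 59.

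The stated 83 lies inside this range but is not reproduced exactly. Nothing below depends on that. What matters is that 83 was computed for one AUC coefficient.

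**2. Separate slopes.** Under the plan's inputs, 41 pairs give about 4.4 events, and a single-cohort slope has simulated Wald power of about 55% to 57%. This leaves out the R² adjustment.

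**3. Noise only, main-effects reading.** Assumptions: no transport effect in either cohort, zero mean shift, change counted in either direction, and 4.5% taken as the healthy event rate. The healthy SD is then 10 / 2.005 = 4.99 s. For a septic SD r times larger, the event rate is 2[1 − Φ(10 / (4.99r))]. The last column is simulated with about 41 per cohort.

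| SD ratio r | Septic event rate | Cohort term significant (Wald) |
|---|---|---|
| 1.25 | 10.9% | about 4% |
| 1.5 | 18.1% | about 27% |
| 2 | 31.6% | about 75% |

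At equal SD the Wald test rejects in well under 1%. The likelihood-ratio test rejects in about 9% to 10% there, so its higher figures (about 55% at ratio 1.5) are partly small-sample inflation.

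**4. Adding the product term to the 10 s model.** With equal true non-zero slopes and a septic SD twice as large, the logistic interaction is falsely significant in about 19%. The figure depends on the setting: a check with common slopes of 3 and 5 s per SD and mean shifts of 0 and 3 s gave 7% to 22% by Wald. The continuous CT difference with robust errors stays at about 5% throughout.

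Power is also low. For slopes of 2 versus 5 s per SD of AUC with equal SDs of about 5 s, the logistic interaction detects the difference in about 8% and the continuous interaction in about 72%. On the log-odds scale, with 0.045 at mean AUC in both cohorts and a mean slope of 1.73, power at N = 83 is 9%, 17% and 30% for slope ratios of 1.5, 2 and 3.

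**5. Detectable slope difference on the continuous scale.** At 80% power with 41.5 per cohort and AUC spread alike in both, it is 2.80 × 4.99 × √((1 + r²) / 41.5):
- r = 1: 13.97 × √(2 / 41.5) = 3.07 s per SD of AUC.
- r = 1.5: 13.97 × √(3.25 / 41.5) = 3.91 s.
- r = 2: 13.97 × √(5 / 41.5) = 4.85 s.

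Power for slopes of 2 versus 5 s correspondingly falls from about 72% to about 51% and 36%.

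**The case against.** The case on the other side has several parts.

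- **The logistic model serves the primary objective.** Section 2.7.7 ties it to AUC and a clinically significant CT change. Section 2.6 speaks of correlating differences in test results with AUC, which suggests a continuous analysis for the secondary question. This stands: a reader might infer that the protocol assigns susceptibility to the 10 s model, and it does not say so. It states no other outcome model either, and section 2.6 does not mention comparing cohorts.
- **The covariate sentence may mean separate slopes.** This stands, and under that reading the criticism of a cohort main effect falls away. The missing comparison of slopes remains.
- **An analysis plan not shown may name the interaction.** It may. The endpoint and model are already fixed here, however, and a product term in the same 10 s model has little power and is open to inflation.
- **The noise figures rest on assumptions.** This stands. A reader might infer that septic CT is known to be noisier, but no section gives a CT, an SD or an anticoagulant effect on the ExTest. At ratio 1.25 the Wald test stays below its nominal 5%. If 4.5% is the pooled rate instead of the healthy rate, Wald rejects in under 1% at ratios 1.5 and 2, while the likelihood ratio still rejects in 49% and 71%.
- **Low power for the cohort contrast breaks no promise.** This stands. The 80% was claimed for one AUC coefficient and the contrast is exploratory. Nor is it the only reason for enrolling septic patients: section 2.5 also cites their need for rapid diagnostics.

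**Conclusion.** The concern holds in a limited form. The article asks about a slope difference, and the one outcome model that it states does not provide a test of it under either reading. Testing the interaction on the signed CT difference, which the trial already collects, answers the question directly. It gives about 72% against 8% power in the example with equal SDs, and about 5% false positives when the SDs differ.

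The risk of a cohort effect made by noise is conditional. It is negligible at an SD ratio of 1.25 and large at 2, given a 4.5% healthy event rate, zero mean shift and changes counted in both directions. The documents do not show which ratio applies, so they do not support the stronger inference that the trial will report a false susceptibility effect. They also do not support reading the sample size as a failed promise of power for the cohort comparison. The point should be settled before analysis and does not affect the primary endpoint.

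**What to change.** 1. Keep the logistic model of the 10 s event for the primary analysis, and reword the covariate sentence to say whether cohort enters as a main effect or through separate AUC slopes.
2. Test susceptibility by the AUC-by-cohort interaction in a linear model of the signed CT difference (pneumatic tube minus manual), with cohort-specific residual variance or robust standard errors. Repeat it on the log CT ratio as a sensitivity analysis.
3. State that a cohort main effect on the 10 s event will not be read as susceptibility to force.
4. Label the comparison exploratory and give its detectable slope difference as a range: about 3.1, 3.9 and 4.9 s per SD of AUC at 80% power for septic:healthy SD ratios of 1, 1.5 and 2, assuming a healthy SD of 5 s.

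The cost is analysis wording and a little extra analysis work, with no new samples, measurements or participants. The downside is a secondary result on a different scale from the binary endpoint, which the report would need to explain.

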### Quantifying acceleration forces

2.6

During transport, speed and acceleration are continuously recorded via a data logger. For this purpose, a three-axis accelerometer (MSR 145, MSR Electronics, Switzerland) (Figure 2) will be transported alongside the sample. This enables the measurement of acceleration along three spatial axes with a sampling rate of 1 kHz, storing the highest recorded value at 50 Hz. Owing to its lightweight and miniaturized design, the sensor can be easily transported within the PTS. The digital analysis of recorded data allows visualization of acceleration throughout transport (Figure 3A). The forces acting during transport can be graphically represented as the area under the curve (AUC) value for each transport instance (Figure 3C). Specifically, acceleration during transport is quantified by calculating the AUC, with a modification to the approach of Streichert et al. (28). This involves classifying absolute vector values into bins, similar to a histogram (Figure 3B), as described by Streichert et al. (28). The values exceeding a predefined acceleration threshold are subsequently summed (cutoff in Figure 3C). The threshold acceleration is defined as the typical acceleration occurring during manual transport. In contrast to Streichert et al. (28), the AUC calculation in the VETaPT trial involves dividing the result by the accelerometer’s sampling rate. This adjustment ensures generalizability, as otherwise, the AUC would be dependent on the sampling rate of the accelerometer. The AUC is calculated as follows:

$$\mathrm{AUC}=\frac{1}{f}*\sum_{i_{0}}n_{i}*\frac{\left(a_{u,i}+a_{l,i}\right)}{2}$$

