where f represents the accelerometer sampling rate and where i_0_ denotes the index of the first bin exceeding the acceleration threshold. Within the sum operator, for each bin i, the product of the number of counts (n_i_) and its mean acceleration, which is calculated as the mean of the upper (a_u,i_) and lower (a_l,i_) bin edges, are multiplied. The formula provided above yields results equivalent to numerically integrating the pure acceleration curve (Figure 3A) while considering only accelerations exceeding the chosen threshold. This approach enables the correlation of differences in coagulation test results between transport methods with their respective AUC values. Consequently, the assumed relationship between acceleration forces and coagulation test results should become evident across different acceleration levels and PTS compressor settings. This method replaces the commonly used yet imprecise characterization of acting forces on the basis of average transport speed with a more methodologically robust and physically accurate approach. By doing so, the acceleration forces—one of the key parameters influencing coagulation activation—are quantified in a standardized and comparable manner. The measured AUC value thereby serves as a parameter that captures the total magnitude of forces exerted by the PTS.

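### The sample size places manual transport at the mean AUC and PTS at mean plus one SD, but every analysed pair carries a PTS AUC, so the stated 80% power does not follow from the inputs

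*Protocol article*

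**What the plan says.** Section 2.7.7 (Sample size and statistical analysis) plans a logistic regression. The outcome is binary: a clotting time change of at least 10 s between the manual and the PTS sample of one participant. The regressor is the AUC, considered in both cohorts.

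The G*Power inputs are two event probabilities:
- The null value applies "when the AUC is at its mean value, i.e., manual transport, where no significant effect is expected", and "this probability is estimated at 0.045".
- The alternative value, 0.21, applies "when the AUC is at its mean plus one standard deviation, i.e., PTS transport, where an effect is expected". It is derived from published clotting time differences between the two transport methods.

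The remaining inputs are "significance level (*α*) = 0.05", "power (1-*β*) = 0.8" and "two-sided test; R^2^ other X = 0.36", with a Wald Z test. The result is 83 paired comparisons, raised to 92 for dropout.

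Section 2.6 (Quantifying acceleration forces) defines the AUC as a sum over accelerations above a cut-off: "The threshold acceleration is defined as the typical acceleration occurring during manual transport". It says that the method allows "correlation of differences in coagulation test results between transport methods with their respective AUC values". Section 2.2 has acceleration measured during PTS transport.

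**The concern.** In this type of calculation the two probabilities belong at the mean, and at one SD above the mean, of the regressor in the rows that will be analysed. Here those rows are pairs. A manual sample has no outcome of its own, because the outcome is the difference between the two samples. The regressor for each pair is the AUC of its PTS run, so its mean is an average PTS transport.

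Manual transport cannot be that mean. The cut-off is set at the typical manual acceleration, which puts manual transport low on the AUC scale. The published manual-versus-PTS contrast has therefore been entered as a gradient per SD among PTS runs, and nothing in the article supports a gradient of that size.

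At stake is the only sample size and power statement in the article, made for the objective that section 2.7.7 calls primary.

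**Working it through.** **1. What the stated inputs imply**
- logit(0.045) = −3.055 and logit(0.21) = −1.325.
- The log odds ratio per SD is −1.325 + 3.055 = 1.730, so the odds ratio is e^1.730 = 5.64.
- With a normal AUC, averaging the event probability over this curve gives 0.107, which is 0.107 × 83 ≈ 9 events.
- If all 83 pairs are PTS pairs at the plan's own 0.21, about 0.21 × 83 = 17 events are expected. The two figures describe the same 83 pairs and do not agree.

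**2. The plan's own N**

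Two-sided α of 0.05, power 0.80, normal AUC, N divided by (1 − 0.36):
- Hsieh: (1.960 + 0.842)² / [0.045 × 0.955 × 1.730²] / 0.64 = 95.3.
- Demidenko without variance correction: 102.8.
- Demidenko with full variance correction: 58.1. A half-weight correction gives about 81.

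The stated 83 lies inside this range of 58 to 103. The article gives neither the distribution of X nor the procedure option, so 83 is neither confirmed nor refuted by arithmetic. Simulated Wald power for the stated inputs at N = 83 is about 84% to 86%. The problem is where the inputs are placed.

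**3. Power with the anchors moved**

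Assumptions, none of them given in the article: probability 0.21 at the mean PTS AUC, 0.045 at AUC about 0, log odds linear in AUC, and AUC normal. The distance from AUC 0 to the mean is then 1/CV standard deviations, where CV = SD/mean of the PTS AUC. The slope per SD is therefore 1.730 × CV, for example 1.730 × 0.5 = 0.865 (odds ratio 2.4) at CV 0.5.

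Simulated power of the Wald test with 83 pairs:

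| CV of PTS AUC | R² = 0.36 | R² = 0 |
|---|---|---|
| 0.3 | 32% | 47% |
| 0.4 | 49% | 68% |
| 0.5 | 69% | 85% |
| 0.6 | 82% | 94% |
| 0.8 | 95% | 99% |

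Closed-form methods at R² = 0.36 bracket the simulation: 31–36% at CV 0.3, 47–56% at 0.4, 61–73% at 0.5 and 72–87% at 0.6. Power reaches 80% between CV 0.5 and 0.6 with R² = 0.36, and between 0.4 and 0.5 with R² = 0.

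**4. Could manual transports be rows of their own?**

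If manual and PTS transports were pooled half and half as a binary X, manual would lie one SD below the mean and PTS one SD above it. The required N would be about 173 to 240. This reading does not lead to 83 either, and it conflicts with an outcome defined per pair.

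**The case against.** **Direction.** A reader might infer that the trial is underpowered. The article does not support that. Section 2.4 deliberately widens the AUC: speed and bag or insert are randomised, there are two pathways, and traffic varies. A CV of 0.6 or more is possible, and power would then exceed 80%. Because speed and bag or insert are randomised, AUC may also correlate little with cohort, which makes the R² = 0 column at least as relevant. The shape of the AUC distribution matters too: with R² = 0, a lognormal AUC gives 76% at CV 0.4 and 89% at CV 0.5. All of this stands.

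**Manual AUC.** It is low but not shown to be zero. The cut-off is the typical manual acceleration, not the maximum, and values above it count in full. If manual AUC is a fraction f of the mean PTS AUC, the slope per SD becomes 1.730 × CV/(1 − f). With f = 0.2 (an assumption), CV 0.4 behaves like 0.4/0.8 = 0.5. Under its own assumptions the table is then somewhat pessimistic. This stands as well.

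**Position of 0.21.** The article ties it to increased AUC in PTS transport and cites sources not available here. Placing it at the mean PTS AUC is the natural reading of a figure equated with PTS transport, but it remains an assumption.

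**Outcome scale.** A reader might infer that analysing clotting time difference as continuous would remove the problem. That is not shown, since power for a slope on AUC depends on the spread of AUC there too.

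None of these points reconciles the stated anchors with the regressor that will be analysed.

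**Conclusion.** The anchors in section 2.7.7 do not match the regressor, so 80% power with 83 pairs does not follow from the stated inputs. This rests on the article's text: one outcome per pair, acceleration logged in PTS runs, and a cut-off at the typical manual level.

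The size and direction of the error are open. Under the assumptions in the working, power runs from about 32% to 95% for CV 0.3 to 0.8 with R² = 0.36, and from about 47% to 99% with R² = 0. It is somewhat higher if manual AUC is not negligible. The deciding quantity, the CV of PTS AUC, is not used in the calculation. This is not proof that the trial is too small, nor that 83 was miscalculated from its inputs.

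**What to change.** Rewrite the sample size paragraph as follows:
- Anchor both probabilities to the PTS AUC distribution: the manual figure at the manual AUC, and the PTS figure at the mean PTS AUC unless its source supports another position.
- Derive the odds ratio per SD from the mean and SD of AUC in logged transports. Runs with the data logger alone would serve.
- State the G*Power X distribution and procedure option, so that the calculation can be repeated.
- Replace the flat 80% claim with power for 83 pairs across a range of AUC CV.

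No increase in N and no change to conduct is requested. The cost is one paragraph and the AUC summary from logged transports. The stated power may become less favourable.
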